## 8.4 Population used in analyses

The primary analysis will be conducted on all participants who have received at least one vaccine dose. Participants withdrawing for reasons related to the primary outcome measure, their last observation will be used in all subsequent analyses (LOCF).

Per protocol analysis of the secondary and exploratory outcome measures will be performed on all vaccinated subjects for whom serum samples are available.

## 8.5 Specific analyses

As mentioned above, the last observation of participants withdrawing for reasons related to the primary outcome measure will be carried forward. The proportion of participants that received three vaccine doses without experiencing side effects will be estimated by the Kaplan-Meier product-limit method.

## 8.6 Statistical Methods

The analysis shall be descriptive as the sample size does not allow any comparison between groups. For categorical variables, frequency distributions, by vaccination group, will be presented. For continuous variables, box-whisker plots, medians, inter-quartile ranges and ranges will be presented by vaccine group.

The proportion of participants that received three vaccine doses without experiencing (serious) side effects will be estimated by the Kaplan-Meier product-limit method, with time as a discrete variable.

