| Secondary Evaluation Criteria | 
The humoral response to the vaccine antigens will be assessed by measuring the level of
 
 
a) Total IgG and IgG isotypes on Days 0, 28, 56, 84, and 365.
 
b) Antigen specific memory B-cell by ELISPOT on Days 0, 84, and 365
 
                                                                                                                                                                                                                                                                                                                                                                                                                                                                                                                                                                                                                                                                                                                                                                  |
| Statistical Methods           | 95% confidence intervals will be calculated for incidence of adverse events and for immune responses within each group. The analysis shall be primarily descriptive.                                                                                                                                                                                                                                                                                                                                                                                                                                                                                                                                                                                                                                                                                                                                                                                                                                                                                                |

[figure not shown]

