### 1.8.3 Rationale for dosage selection

Studies with either MSP3 or GLURP as Long Synthetic Peptides indicate that both peptides induce a dose-dependent immunological response. This study intends to evaluate previously used 100µg of GMZ2 as well 30µg of GMZ2 as this is the first time the product will be tested in children. This approach will allow for identification of any dose dependant toxicity of the product and also determination of the safest dose of the vaccine that is immunogenic in a population close to the targeted Expanded Program of Immunization (EPI) age group.

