## 2 OBJECTIVES

### 2.1 Primary Objective

**To evaluate the safety and reactogenicity** of three doses of 30 and 100µg GMZ2, adsorbed on aluminium hydroxide, in comparison with three doses of the control vaccine (rabies), in healthy Gabonese children aged 1-5 years. This will be done through evaluation of the following:

1. Immediate reactogenicity; defined as any systemic adverse reactions occurring within 30 minutes after each injection,
2. Local and systemic reactogenicity measured from Day 0 to Day 14 after each dose,
3. Any unsolicited Adverse Event resulting in a visit to a physician between each injection and one month after the third dose,
4. Any Serious Adverse Event (SAE) occurring from the inclusion throughout the study.

Biological safety, one month after each vaccination, in reference with the baseline level the following :

1. RBC, haemoglobin, haematocrit, platelets and WBCs
2. Creatinine, ASAT, ALAT, total bilirubin and alkaline phosphatase.

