## 8 STATISTICAL METHODS AND DATA ANALYSIS

### 8.1 Principal Objective

To evaluate the safety of three doses of 30 µg and 100 µg GMZ2 adjuvanted with alum hydroxide and given at D0, D28 and D56, in healthy children aged 1-5 years old in Gabon.

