### 8.2 Determination of the Sample Size

The total number of participants will be 30 divided into three groups of 10 each; one receiving 30 µg of GMZ 2, another 100 µg of GMZ2 and the other receiving rabies vaccine (control vaccine). The sample size chosen for this study are in line with similar safety and immunogenicity studies of similar candidate malaria vaccines published in the literature. As a phase I protocol, this study of 30 volunteers is not designed to detect adverse reactions that occur infrequently. Sample size was determined by the requirement to make a preliminary evaluation of inter-group and inter-individual variability, to avoid excessive risk and to allow realistic workload. Statistical significance may not be reached in such a study with low power; however, a non-significant finding would provide justification of the need for a study with greater power.

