### 8.6.1 Primary Criterion

The null hypothesis for the primary outcome measure will be evaluated using a one-sample one-sided test for proportions. The null hypothesis states that the frequency of serious adverse reactions is equal among each of the three groups (30 µg GMZ2, 100 µg GMZ2 and rabies vaccinated group). The alternative hypothesis states that this frequency is greater than 25% in the GMZ2 groups.

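### The primary objective compares the safety of each GMZ2 dose with rabies vaccine, but the planned analysis rules out between-group comparison and estimates no safety difference from rabies

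*Protocol*

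**What the plan says.** All references are to the protocol; no SAP is at hand.

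- **2.1 Primary Objective**, repeated in the synopsis: safety and reactogenicity of both GMZ2 doses are to be evaluated "in comparison with three doses of the control vaccine (rabies), in healthy Gabonese children aged 1-5 years".
- **8.1 Principal Objective**: "To evaluate the safety of three doses of 30 µg and 100 µg GMZ2 adjuvanted with alum hydroxide". The rabies arm is not mentioned.
- **Synopsis, Statistical Methods**: "95% confidence intervals will be calculated for incidence of adverse events and for immune responses within each group".
- **8.6 Statistical Methods**: "The analysis shall be descriptive as the sample size does not allow any comparison between groups". Frequencies, medians and Kaplan-Meier proportions follow, with summaries presented by vaccine group.
- **8.6.1 Primary Criterion**: "The null hypothesis states that the frequency of serious adverse reactions is equal among each of the three groups". The null is to be "evaluated using a one-sample one-sided test for proportions", with the alternative that the frequency exceeds 25% in the GMZ2 groups.
- **8.6.2 Secondary Criteria**: no hypothesis tests, but point estimates with 95% intervals, which are meant to let immunogenicity be compared across the three groups.
- **8.2 Determination of the Sample Size**: 30 children, 10 per arm, chosen partly to get a first view of variation between groups. It grants that power is low and adds that "a non-significant finding would provide justification of the need for a study with greater power".
- **1.8.3 Rationale for dosage selection**, on testing two doses: "This approach will allow for identification of any dose dependant toxicity of the product".

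Section 3.1 calls the analysis after Day 84 the primary one and uses it for the decision on the next paediatric trial.

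**The concern.** An objective framed as a comparison with a concurrent control needs an analysis that sets the two arms against each other. Here the objective has a comparator, its restatement in the statistics chapter does not, and the methods text forbids comparison. The reason given is sample size. That reason bears on power and precision, not on whether a difference can be estimated, and 8.6.2 does not apply it to the immune responses of the same 30 children.

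At stake is what the Day-84 report can say about the primary objective. Done as written, it would hold three separate sets of frequencies and within-group intervals, plus a test of the GMZ2 arms against a fixed 25%. It would hold no estimate, with its uncertainty, of how much more often children react to GMZ2 than to rabies vaccine.

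**Working it through.** **1. The plan's own figure.** 3 arms × 10 = 30, which agrees with 8.2. That section gives no alpha, power or effect size, so nothing further can be reproduced. The event counts and rates below are assumptions.

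**2. What each planned output says about GMZ2 versus rabies.**

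| Planned output | Uses rabies data? | Gives a GMZ2–rabies contrast? |
|---|---|---|
| Frequencies by group (8.6) | yes | no, side by side only |
| 95% CIs within each group (synopsis) | yes | no |
| Kaplan-Meier proportions (8.5, 8.6) | not stated by arm | no |
| One-sample test against 25% (8.6.1) | no | no |

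**3. The 8.6.1 test.** With n = 10 and the exact binomial, P(X ≥ 6 | 0.25) = 0.0197 and P(X ≥ 5 | 0.25) = 0.078. The cut-off is therefore 6 of 10 at an assumed one-sided level of either 0.05 or 0.025. The rabies count enters nowhere, so the test cannot address its own null of equality across three groups. It is also confined to serious adverse reactions, whereas 2.1 covers immediate, local and systemic reactogenicity, medically attended events, SAEs and laboratory safety.

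**4. Can a difference be estimated at 10 per arm?** Newcombe interval for d = p1 − p2, with Wilson limits (l, u) for each arm:

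- lower = d − √[(p1 − l1)² + (u2 − p2)²]
- upper = d + √[(u1 − p1)² + (p2 − l2)²]

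For 7/10 v 1/10 the Wilson limits are 0.397–0.892 and 0.018–0.404, and d = 0.60.

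- lower = 0.60 − √[(0.303)² + (0.304)²] = 0.60 − 0.43 = 0.17
- upper = 0.60 + √[(0.192)² + (0.082)²] = 0.60 + 0.21 = 0.81

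The exact (Clopper-Pearson) within-group intervals are 35–93% and 0.3–45%. They overlap, although the interval for the difference excludes 0 (Fisher p = 0.020).

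Precision when the arms agree: 0/10 v 0/10 gives ±28 points, 3/10 v 3/10 gives ±36, and 5/10 v 5/10 gives ±37.

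**5. How often would a difference show?** Full enumeration of the binomial outcomes, 10 v 10:

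| Assumed true rates | Exact within-group CIs do not overlap | Newcombe CI above 0 | Fisher two-sided p ≤ 0.05, same direction |
|---|---|---|---|
| 60% v 10% | 15% | 66% | 47% |
| 70% v 20% | 12% | 62% | 43% |
| 40% v 10% | 2% | 29% | 15% |
| 30% v 10% | 0.4% | 14% | 6% |
| 25% v 5% | 0.2% | 14% | 5% |

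With equal true rates of 10%, 30% and 50%, the Newcombe interval lies above 0 in 0.5%, 1.9% and 2.1% of trials.

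**6. Scale.** Detecting 25% v 5% with 80% power at two-sided 0.05 needs 49 per arm (59 with continuity correction). Section 8.6 is right that a powered test is out of reach. It does not follow that no comparison can be made.

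**The case against.** The strongest reply is that this is a phase I trial with 10 per arm that openly declares a descriptive analysis and low power. Frequencies shown next to a concurrent rabies arm are themselves a comparison of a kind. The background section justifies the control arm mainly by the need to interpret serology. Anyone with the published counts can compute a risk difference, and the form of an interval is often left to the SAP, which 8.7.1 promises. Rewording 2.1 as descriptive would also cure the mismatch.

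Much of that stands. Low power is not an error here, and a descriptive analysis is a legitimate choice. What remains is that 8.6 does not leave the contrast open for the SAP but excludes it, for a reason that 8.6.2 contradicts. Section 8.7.1 also ties the SAP to the final database lock, while the decision-making analysis comes after Day 84.

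Some stronger readings go too far:

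- A reader might infer that the plan names no between-group contrast at all. It does: 8.6.1 states equality across three groups, though only for serious adverse reactions and with a test that cannot address it.
- A reader might infer that the safety conclusion could be picked afterwards from pooled or separate contrasts. No pooled contrast is planned and all arms are reported.
- A reader might take 100 v 30 µg as a promised primary contrast. Section 1.8.3 is dose rationale, not an objective.
- The protocol nowhere tells readers to judge by overlap of intervals, and the large gain at 60% v 10% depends on a 50-point difference and on setting a conservative interval against a less conservative one.

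**Conclusion.** The point holds as a contradiction within the protocol. Section 2.1 compares with rabies, 8.1 omits rabies, 8.6 forbids comparison, and 8.6.1 states a three-group null that its one-sample test cannot address. As written, the primary objective receives no estimated safety contrast with rabies vaccine.

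The gain from adding one is real but limited. At 50-point true differences the interval for the difference would lie above 0 in about 62–66% of trials; at 25% v 5% or 30% v 10% in about 14%, and at 40% v 10% in 29%. The case for estimating the difference is that it answers the stated objective and shows the uncertainty, not that it makes a small trial sensitive. These figures rest on assumed event rates, 10 evaluable children per arm and the Newcombe interval. This should be corrected, but it does not undermine the design.

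**What to change.** In one amendment:

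1. **8.1**: restore the rabies comparator so that it matches 2.1.
2. **8.6**: replace the quoted sentence by: *The analysis is descriptive. For each primary safety criterion, the differences 30 µg minus rabies and 100 µg minus rabies in the proportion of children with at least one event will be given with two-sided 95% CIs (Newcombe), without significance claims or multiplicity adjustment; 100 minus 30 µg is given as supportive.* For the laboratory criterion, an event can be the clinically significant abnormality that 6.1.5 already has recorded.
3. **Synopsis**: make the same change.
4. **8.6.1**: remove the test, or make its null, alternative and test agree. Left as it is, a hypothesis test would stand directly below text that disclaims significance.
5. **8.2**: replace the wording on significant and non-significant findings by the expected precision, about ±36 points at 3/10 v 3/10.

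If the sponsor does not want a contrast, the minimum is to reword 2.1 and the synopsis as description by group with rabies as context, and still to carry out items 4 and 5.

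The cost is protocol and SAP wording and a few table columns, with no new data or children. The downside is intervals that are visibly wide.

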### 8.6.1 Primary Criterion

The null hypothesis for the primary outcome measure will be evaluated using a one-sample one-sided test for proportions. The null hypothesis states that the frequency of serious adverse reactions is equal among each of the three groups (30 µg GMZ2, 100 µg GMZ2 and rabies vaccinated group). The alternative hypothesis states that this frequency is greater than 25% in the GMZ2 groups.

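### The only hypothesis test on the primary outcome (Protocol 8.6.1) is undefined as written: its test, null and alternative do not fit together

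*Protocol*

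**What the plan says.** Protocol 8.6.1 fixes three things for the primary outcome.

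- Method: the null is to be "evaluated using a one-sample one-sided test for proportions".
- Null: "The null hypothesis states that the frequency of serious adverse reactions is equal among each of the three groups", namely 30 µg GMZ2, 100 µg GMZ2 and rabies vaccine.
- Alternative: "The alternative hypothesis states that this frequency is greater than 25% in the GMZ2 groups".

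It gives no significance level, no test version, no reason for 25%, and no statement on whether the GMZ2 arms are tested singly or together. Section 8.6.2 excludes hypothesis testing for secondary and exploratory outcomes, so this is the only test in the plan.

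The surrounding text points elsewhere. Section 8.6 states: "The analysis shall be descriptive as the sample size does not allow any comparison between groups". The synopsis says "The analysis shall be primarily descriptive" and that "95% confidence intervals will be calculated for incidence of adverse events" within each group. Section 8.2 gives the size ("The total number of participants will be 30 divided into three groups of 10 each"), concedes low power, and adds that "a non-significant finding would provide justification of the need for a study with greater power".

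**The concern.** The three elements of 8.6.1 belong to different tests. A one-sample test compares one observed proportion with a fixed value. Equality of three groups is a between-group hypothesis that needs the rabies data, and 8.6 says the sample cannot support such a comparison. The 25% figure appears only in the alternative, so the null does not supply the reference value that a one-sample test needs.

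This is not a detail left to an analysis plan. The protocol itself fixes the test and both hypotheses, and no analysis plan could carry them out as written. Two analysts could follow 8.6.1 in good faith and report opposite results from the same children. On one reading, half an arm with serious reactions would be reported as non-significant, which invites misreading.

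**Working it through.** **Inputs.** From 8.2: n = 10 per arm, so 20 on GMZ2 if pooled. From 8.6.1: the 25% threshold and the one-sided direction. Assumed: exact binomial test at one-sided 5%, with 2.5% as the range. The protocol states no power or critical value for this test, so there is no figure to reproduce.

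**1. Do the hypotheses partition the possibilities?**

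- GMZ2 20%, rabies 0%: the groups are unequal and GMZ2 is not above 25%. Neither hypothesis holds.
- All three groups at 40%: the groups are equal and GMZ2 is above 25%. Both hypotheses hold.

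In the second case the stated null is true, yet a 25% test rejects with probability 0.166 in one arm, 1 − (1 − 0.166)² = 0.30 in at least one of two arms, and 0.404 pooled. The assumed 5% level is not held under the stated null.

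**2. The one testable reading: p ≤ 25% against p > 25%.**

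P(X ≥ r) = Σ C(n,k) p^k (1 − p)^(n − k), summed over k = r to n.

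- n = 10, p = 0.25: P(X ≥ 5) = 0.078 and P(X ≥ 6) = 0.020. Reject at 6/10 or more, at either 5% or 2.5%.
- n = 20, p = 0.25: P(X ≥ 8) = 0.102, P(X ≥ 9) = 0.041 and P(X ≥ 10) = 0.014. Reject at 9/20 or more at 5%, and at 10/20 or more at 2.5%.

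Power at one-sided 5%:

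| True rate | One arm (6/10 or more) | Pooled (9/20 or more) |
|---|---|---|
| 40% | 17% | 40% |
| 50% | 38% | 75% |
| 60% | 63% | 94% |

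At 2.5% the per-arm figures do not change; pooled power falls to 24% at a true 40% and 59% at 50%.

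The largest non-significant count in one arm is 5/10, with a Clopper-Pearson 95% interval of 19% to 81%. The test version matters at that count: z = (0.50 − 0.25)/√(0.25 × 0.75/10) = 1.83 gives P = 0.034 uncorrected, but 0.072 with continuity correction and 0.078 exact.

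**3. The equality reading.** For 4/10 on GMZ2 against 0/10 on rabies, one-sided Fisher P = C(10,4)/C(20,4) = 210/4845 = 0.043, which rejects. The same 4/10 does not reach the 6/10 needed in step 2.

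**4. Can a clean arm exclude 25%?** The upper limit for 0/n is 1 − a^(1/n).

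- 0/10: 1 − 0.025^(1/10) = 30.8% (two-sided 95%) and 1 − 0.05^(1/10) = 25.9% (one-sided 95%). Equivalently, 0.75^10 = 0.056. Neither limit excludes 25%.
- 0/20 pooled: 1 − 0.025^(1/20) = 16.8%, which does.

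**The case against.** The best defence is that this is a small phase I study whose analysis is essentially descriptive. Within-group 95% intervals are already planned in the synopsis, and 8.5 and 8.6 add Kaplan-Meier estimates and frequency distributions. A one-sample test against 25% is not in itself a between-group comparison, and the synopsis's wording is compatible with one such test. Serious events are also handled outside this test, through reports to the safety board and the local safety monitor (6.2.1, 6.2.2). All of that stands. It limits the consequence but does not make 8.6.1 coherent.

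It also rules out stronger readings that a reader might infer:

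- *The test is biased towards a verdict of safe.* No section equates non-rejection with safety, and 8.2 treats a non-significant result as inconclusive. The error can also run the other way, as step 1 shows.
- *This is the only inference on the primary outcome.* It is the only hypothesis test; the planned intervals are inference too.
- *The synopsis also bars group comparison.* Only 8.6 does.
- *The decision on the next trial rests on this test.* Sections 3.1 and 8.7.1 tie that decision to the Day 84 results and the immediate safety profile, without mentioning the test.
- *Non-significance is the expected result at any unacceptable rate.* Pooled power at a true 50% is 75%. Even tested singly, at least one of two independent arms would reject with probability 1 − 0.623² = 61%.

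**Conclusion.** Wrong as written. The mismatch between test, null and alternative, and the conflict between the three-group null and 8.6, follow from the text alone and need no assumption. The figures depend on an exact test at one-sided 5%, which is assumed. At 2.5% the per-arm rule is unchanged and the pooled cut-off rises by one child.

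The practical size is that the two readings diverge at counts such as 4/10 against 0/10, and that on the 25% reading as many as 5 of 10 children in an arm could have serious reactions without significance. Non-rejection would therefore be no evidence of safety. The protocol does not claim that it would be.

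**What to change.** Before the Day 84 data lock, delete the test and both hypotheses from 8.6.1. Report instead the number and proportion of children with serious adverse reactions, and with each other primary safety outcome, per arm and for the two GMZ2 arms pooled, with Clopper-Pearson 95% intervals. This agrees with 8.6 and makes the synopsis's within-group intervals specific.

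If 25% is kept as a benchmark, give its justification and state one coherent hypothesis pair with its significance level, its unit (per arm or pooled) and an exact method. Say also that 0/10 does not exclude 25%.

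Keep the low-power caveat in 8.2; reword its reference to a non-significant finding only if no test remains. Risk differences against rabies are optional. They suit the comparative primary objective in 2.1, but 8.6 would then have to be reconciled with that objective.

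The cost is protocol and analysis-plan wording only: no extra children, visits, samples or data.
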